### Statistical considerations

#### Sample size

We used a definition of a clinically important difference for the SF-36 physical function subscale from three expert consensus panels for chronic diseases in adults. The panels conducted a literature search and used the Delphi technique to reach consensus on the thresholds for change over time for small, moderate and large clinically important SF-36 change scores [24]. Consensus was agreed by each panel that a small clinically important difference would be 10 as this is the equivalent to two state changes (a state change is one improvement in one item - the minimum difference between inventories). A moderate improvement was defined as 20 and a large improvement as 30.

To be able to detect a difference between the two treatment arms of 8 to 10 points on the SF-36 PCS at six months with 90% power and 1% two-sided alpha, we have calculated (using STATA) that a total of 32 to 50 participants in each arm for analysis are required. Allowing for 10 to 20% non collection of primary outcome data at six months, we aim to recruit 80 to 112 participants to the study.

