#### Primary outcome

The primary outcome will be the SF-36 physical function subscale analysed as a continuous variable collected at six months post-randomisation. The SF-36 will be scored as the sum of responses to the ten items, each of which is coded 0 for ‘Yes, limited a lot’, 5 for ‘Yes, limited a little’ and 10 for ‘No, not limited at all’. This yields a score varying from 0 (for the highest level of disability) to 100 for no disability. The SF-36 physical function subscale will be used as we are primarily interested in change in physical function. It has been used in studies of adolescent CFS/ME [22] and in CFS trials in adults [16]. We chose six months as this was the first time that all those randomised to LP and SMC will have received LP. Secondary outcome measures will be school attendance, calculated as a percentage of expected sessions, at 3, 6 and 12 months; the SF-36 (physical function) at 3 and 12 months; the Chalder Fatigue Scale score at 3, 6 and 12 months; pain visual analogue scale at 6 months and quality adjusted life years (QALYs, derived from the EQ-5D) over the 12 month follow- up period.

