### Data monitoring

The data monitoring group will receive notice of serious adverse events (SAEs) for the sample as whole. If the incidence of SAEs of a similar type is greater than would be expected in this population, it will be possible for the data monitoring group to receive data according to trial arm to determine any evidence of excess in either arm.

Primary outcome data at six months will be examined once data are available from 50 patients, to ensure that neither arm is having a detrimental effect on the majority of patients. An independent statistician with no other involvement in the study will investigate whether more than 20 participants in the study sample as a whole have experienced a reduction of ≥ 30 points on the SF-36 at six months. In this case, the data will then be summarised separately by trial arm, and sent to the data monitoring group for review. This process will ensure that the trial team will not have access to the outcome data separated by treatment arm.

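### The only power statement names the SF-36 PCS and needs an SD of about 10, so 90% power is not shown for the primary outcome, the 0-100 physical function subscale

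*Protocol article*

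**What the plan says.** The Primary outcome section is explicit: "The primary outcome will be the SF-36 physical function subscale analysed as a continuous variable collected at six months post-randomisation". The score is the sum of ten items coded 0, 5 or 10, and "This yields a score varying from 0 (for the highest level of disability) to 100 for no disability". The Data analysis section compares this same subscale between arms by linear regression, adjusted for its baseline value and the minimisation variables.

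The Sample size section starts from the same measure: "We used a definition of a clinically important difference for the SF-36 physical function subscale from three expert consensus panels". It continues: "Consensus was agreed by each panel that a small clinically important difference would be 10", equivalent to two one-step item changes, and "A moderate improvement was defined as 20 and a large improvement as 30". The next paragraph changes the name of the measure. The trial is to detect "8 to 10 points on the SF-36 PCS at six months with 90% power and 1% two-sided alpha", which is said to need 32 to 50 participants per arm for analysis. Allowing for 10 to 20% missing primary outcome data, this becomes 80 to 112 recruited. No SD, baseline correlation or source of variance accompanies the calculation.

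**The concern.** A power statement has to concern the variable that will be tested. Here the difference is argued for on one measure and the power is stated for another label. That label is used once, is not defined, and is missing from the Abbreviations section.

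The name matters because the sample size depends on the SD as much as on the difference, and an SD belongs to a particular score. A reader cannot tell whether the SD behind 32 to 50 per arm is one for the 0-100 subscale or one for some other score. This statement is the only justification in the article for recruiting 80 to 112 children. If the subscale's SD, after any gain from adjustment, is well above the value used, power for the difference the article treats as clinically important is well below 90%. An inconclusive result would then be weaker evidence than the stated power suggests.

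**Working it through.** **Inputs, all from the Sample size section:** difference 10 points with 32 per arm; difference 8 points with 50 per arm; two-sided alpha 0.01; power 0.90. The SD is not given. These pairings of difference and size are an inference: the larger difference goes with the smaller sample.

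**Step 1. Recover the SD.** For two means with equal allocation, n per arm = 2(z₀.₉₉₅ + z₀.₉₀)² SD²/δ². Here 2 × (2.5758 + 1.2816)² = 29.76.

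- 32 per arm, 10 points: SD = √(32 × 100 / 29.76) = 10.37
- 50 per arm, 8 points: SD = √(50 × 64 / 29.76) = 10.37

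Both ends give the same value, which supports the pairing. Solving with the t distribution instead gives 10.09 and 10.19.

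**Step 2. Forward check.** With SD exactly 10, the t-test needs 32 per arm for 10 points and 49 for 8 points. Power at the stated sizes is 90.6% and 91.2%. With SD 10, a 5% two-sided alpha would need 22 and 33 per arm, and a 1% one-sided alpha 27 and 41 (normal formula), so neither explains the figures.

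**Step 3. Recruitment.** 2 × 32 = 64, and 64/0.8 = 80. 2 × 50 = 100, and 100/0.9 = 111.1, which is 112 in even numbers. The recruitment figures follow.

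The arithmetic is therefore sound given an SD of about 10. The open question is whether that SD belongs to the primary outcome.

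**Step 4. What if it does not?** The documents give no SD for the subscale, so SDs of 15, 20 and 25 are assumptions, as are the baseline correlations r. Because the primary analysis adjusts for baseline, the relevant spread is the residual SD = SD × √(1 − r²). For example, SD 20 with r = 0.5 gives 20 × √0.75 = 17.3. Power is from the non-central t at 1% two-sided:

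| Assumed SD | r | Residual SD | 32 per arm, 10 points | 50 per arm, 8 points | 50 per arm, 10 points |
|---|---|---|---|---|---|
| 15 | none | 15.0 | 51% | 52% | 76% |
| 15 | 0.7 | 10.7 | 86% | 86% | 98% |
| 20 | none | 20.0 | 27% | 27% | 45% |
| 20 | 0.5 | 17.3 | 37% | 38% | 60% |
| 20 | 0.7 | 14.3 | 56% | 57% | 81% |
| 25 | none | 25.0 | 15% | 16% | 27% |
| 25 | 0.5 | 21.7 | 22% | 22% | 38% |

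The last column is the most favourable combination within the stated ranges.

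**Step 5. Correlation needed to rescue the claim.** A residual SD of 10 requires r = √(1 − (10/SD)²): 0.75 if the raw SD is 15, 0.87 if it is 20 and 0.92 if it is 25.

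**The case against.** **PCS may be a slip of the pen.** The preceding paragraph takes the difference from the physical function subscale, so the author may have meant that subscale throughout. This is quite possible. Correcting the label would remove the contradiction, but the calculation would still rest on an SD of about 10 for a 0-100 score, with nothing in the article to support it.

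**An article may leave the SD to the full protocol.** That is fair, and a missing SD alone would not be a finding. The point rests on what is printed: a power claim attached to a measure that is not the primary outcome, which leaves the origin of the implied SD ambiguous.

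**Adjustment and the upper sample size could restore much of the power.** This stands. With SD 15 and r = 0.7, power is 86% at both stated pairs and 98% for 50 per arm and 10 points. The Data analysis section also commits to 95% confidence intervals alongside P-values, so imprecision would be visible in the report.

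Two arguments may tempt a reader to go further and say that an SD of 10 is shown to be wrong. Neither succeeds.

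- The consensus thresholds of 10, 20 and 30 would be 1, 2 and 3 SDs if the SD were 10, which looks odd for small, moderate and large. But they are expert thresholds for change over time in adults, and 10 is justified by item steps rather than by spread. They only hint that an SD of 10 is small.
- The Data monitoring rule asks "whether more than 20 participants in the study sample as a whole have experienced a reduction of" 30 points or more, examined once 50 patients have data. With normal changes and no mean change, the chance of more than 20 in 50 is about 2 × 10⁻¹² at a change SD of 20 and 4 × 10⁻⁸ at 25. The event is practically impossible at these larger SDs as well, so the rule cannot tell one SD from another. It is a trigger for harm, not an estimate of variance.

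**Conclusion.** The point holds. The Sample size section must be reconciled with the Primary outcome and Data analysis sections, because the only power claim is stated for a measure that is not the primary outcome. The stated sizes need an SD or residual SD of about 10. Nothing in the article ties that value to the 0-100 subscale, so 90% power for the trial's own endpoint is unsupported.

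A reader might infer that the trial is underpowered. The documents do not establish that, because they contain no subscale SD. Over the assumed SDs of 15 to 25 and the correlations tabulated, power at the two stated pairs runs from 86% down to 15%. At 50 per arm and 10 points it runs from 98% down to 27%. It is certain that the SD must be about 10 to give the stated sizes; the size of any shortfall is conditional on the assumptions.

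**What to change.** In the Sample size section:

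1. Replace SF-36 PCS with the SF-36 physical function subscale (0-100).
2. Redo the calculation with the SD of that subscale, taken from pooled, arm-blind feasibility or baseline data, and with the baseline correlation relied on for the adjusted analysis. Baseline scores alone give an SD but not that correlation, which needs follow-up scores as well.
3. State both values and their source.
4. Restate the power, or the difference detectable with 90% power at 1% two-sided alpha, that 80 to 112 participants deliver after the allowed loss.

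The cost is a recalculation and a wording amendment. Recruitment, endpoint and analysis do not change. The downside is that the stated figure may become less favourable. If the data do show a residual SD near 10, the present sizes stand and only the label and the missing inputs need correcting.

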**Methods:**

This pragmatic randomised controlled trial is set within a specialist paediatric CFS/ME service in the south west of England. Children and young people with CFS/ME (n = 80 to 112), aged 12 to 18 years old will be randomised to specialist medical care (SMC) or SMC plus the LP. The primary outcome will be physical function (SF-36 physical function short form) and fatigue (Chalder Fatigue Scale).

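### The recruitment range of 80 to 112 combines 20% loss at its lower end with only about 10% loss at its upper end, so 112 falls slightly short for 8 points at the 20% loss the plan allows for

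*Protocol article*

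**What the plan says.** The sample size section of the protocol article sets out its calculation as a series of ranges. The target is 8 to 10 points on the SF-36 at six months, and the calculation is made "with 90% power and 1% two-sided alpha". From this the authors conclude that "a total of 32 to 50 participants in each arm for analysis are required". The larger number belongs to the smaller difference, so 50 per arm goes with 8 points and 32 per arm with 10 points. The recruitment figure follows: "Allowing for 10 to 20% non collection of primary outcome data at six months, we aim to recruit 80 to 112 participants". The Methods part of the abstract repeats the range: "Children and young people with CFS/ME (n = 80 to 112".

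The section does not say which loss rate was applied to which requirement, and it gives no standard deviation.

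**The concern.** A reader would take the loss sentence to mean that the recruitment range absorbs 10 to 20% missing primary outcome data for the differences just named. If so, the upper end should protect the 8-point requirement at up to 20% loss. It does not: the upper end was inflated for the lowest loss in the stated range, while the lower end was inflated for the highest.

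At stake is how far the 90% power statement can be relied on. For 8 points it holds at 112 recruited only near the favourable end of the loss range. A reader of the article cannot see this without redoing the arithmetic.

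**Working it through.** **Inputs from the sample size section.** Analysed per arm: 32 (10 points) and 50 (8 points), so 64 and 100 in total. Loss: 10% to 20%. Recruitment: 80 to 112. Power 90%, two-sided alpha 1%. Assumption: 1:1 allocation, implied by a single number per arm.

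**Step 1: reproduce the plan's range.** Recruited N = analysed N / (1 − loss).

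| Requirement | 10% loss | 20% loss |
|---|---|---|
| 64 analysed (10 points) | 64/0.90 = 71.1, so 72 | 64/0.80 = 80 |
| 100 analysed (8 points) | 100/0.90 = 111.1, so 112 with equal arms | 100/0.80 = 125, or 126 with equal arms |

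The published ends are the top-right and bottom-left cells. Working backwards, 80 implies a loss of 1 − 64/80 = 20.0%, and 112 implies 1 − 100/112 = 10.7%, so no single loss rate gives both. Inflating by multiplication does not give them either: 64 × 1.1 = 70.4, 64 × 1.2 = 76.8, 100 × 1.1 = 110, 100 × 1.2 = 120.

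**Step 2: what 112 leaves for analysis.** This step needs no SD.
- 10% loss: 112 × 0.90 / 2 = 50.4 per arm (meets 50)
- 15% loss: 112 × 0.85 / 2 = 47.6 per arm
- 20% loss: 112 × 0.80 / 2 = 44.8 per arm

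The requirement of 50 per arm is therefore missed once loss exceeds 10.7%.

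**Step 3: the implied SD.** With the normal approximation, n per arm = 2 SD² (2.576 + 1.282)² / difference². For n = 50 and 8 points, SD = 10.37; for n = 32 and 10 points, also 10.37, because 50 × 8² = 32 × 10² = 3,200. With a noncentral t calculation the implied SDs are 10.19 and 10.09. A round SD of 10 with the t calculation gives 49 and 32 per arm, close to the stated figures. The range 10.0 to 10.4 is therefore an assumption drawn from the plan's own numbers.

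**Step 4: power for 8 points with 112 recruited and 20% loss (44.8 per arm).** With the normal approximation at SD 10.37: standard error = 10.37 × √(2/44.8) = 2.191; 8/2.191 = 3.651; 3.651 − 2.576 = 1.075; power = 85.9%. Across methods:
- normal, SD 10.37: 85.9%
- t, SD 10.19: 85.7%
- t, SD 10: 87.3%
- normal, SD 10: 88.7%

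The two SD 10 figures stay closer to 90% partly because, at that SD, 50 per arm already gives more than 90% (91.3% by t, 92.3% by the normal approximation).

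**Step 5: the same shortfall in points.** At SD 10.37, the difference detectable with 90% power at 44.8 per arm is 8 × √(50/44.8) = 8.45 points.

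**Step 6: the 10-point target.** With 80 recruited and 20% loss, 80 × 0.80 / 2 = 32 per arm, exactly the stated requirement. With 112 recruited and 20% loss, power for 10 points is about 97 to 98%.

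**The case against.** The strongest reply is that the paragraph lists ranges in sequence and never promises 90% power for every difference at every loss rate and every recruitment figure. This is right, and it limits the point. In particular, a reader might infer that the plan claims 90% power for 8 points with only 80 recruited, and then find power of roughly 68 to 73% at 20% loss under the same SD assumptions. The document does not make that claim: 80 derives from the 10-point requirement. A reader might also infer that the plan is defective for not naming a single recruitment target. That is a preference, and a condensed article may leave the rule for ending recruitment to the full protocol, which is not shown.

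It can also be said that 10 points is the difference the section supports, as the consensus value for a small clinically important change, and that it is protected throughout. This stands, but 8 points is named under the same 90% statement.

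Finally, there is possible mitigation. The data analysis section adjusts for the baseline score; if the planning SD is unadjusted, a baseline correlation of about 0.32 would offset the loss (1 − 0.32² ≈ 0.896 = 44.8/50). No correlation is given, however, and the SD may already allow for adjustment. The reminders, reduced questionnaire set and telephone completion described for non-responders should limit missing data, but they do not guarantee 10%, and the plan itself allows for 20%. Neither feature changes the stated requirement of 50 analysed per arm.

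**Conclusion.** The point holds in a narrow form. The two ends of the recruitment range carry different loss rates without saying so, and at the upper end of the plan's own loss allowance 112 recruited does not supply the 50 per arm required for 8 points. That head count rests only on the document's figures and on equal allocation.

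The size is modest: 44.8 instead of 50 per arm, and about 1 to 4 percentage points of power below 90%. The power figures depend on a back-calculated SD and should be read as a range. The defect is confined to 8 points with loss above about 10.7%. It does not undermine the trial's ability to detect 10 points, and it does not show that the trial is underpowered in general.

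**What to change.** Reword the sample size paragraph to state three things:
- 80 recruited assumes a 10-point difference and up to 20% loss.
- 112 recruited assumes an 8-point difference and about 10% loss.
- At 20% loss, 112 gives slightly under 90% power for 8 points: about 86 to 89% if the SD is about 10.0 to 10.4. The SD actually used should be stated, and this figure recalculated from it.

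The recruitment range can stay as published; no added enrolment is asked for, and conduct and analysis do not change. The cost is a few words and a slightly less favourable power statement for the 8-point difference.

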#### Data analysis

The analysis and presentation of the trial will be in accordance with CONSORT guidelines [14]. A full statistical analysis plan will be developed and agreed with the Trial Management Group and Trial Steering Committee prior to conducting any analyses.

We will use descriptive statistics to compare characteristics of invited individuals who did or did not agree to take part and eligible individuals who were randomised or not randomised. We will also examine the balance between the trial arms in participant characteristics.

The primary intention-to-treat analysis will compare the SF-36 physical function subscale at six months between groups using multivariable linear regression adjusting for baseline value of the outcome and minimisation variables, paying attention to 95% confidence intervals as well as *P*-values. Similar analyses using appropriate regression models will be conducted for secondary outcomes. Sensitivity analyses will be conducted using standard techniques to impute missing data [25], and to estimate the efficacy of the intervention among compliers.

The statistical analysis plan including subgroup analyses for the primary outcome. This will be conducted to explore differences in outcome according to age (< 14.99 versus 15.0 to 17.99), gender (male/female) and severity (no school attendance versus some school attendance) as age and gender are risk factors for CFS/ME and disease severity is a predictor of outcome. These subgroup analyses are exploratory and will be interpreted with due caution [26]. Any suggestion that the intervention effect differs according to age, gender or severity would need to be confirmed in subsequent studies. These will include interaction terms in regression models.

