### Randomisation

The recruiting researcher will explain the rationale for the study and its design, the uncertainties about the effectiveness of either intervention, the known advantages/disadvantages of the interventions, the options available outside the RCT, and the right not to take part in the study or to withdraw at any time. Willingness to participate will be ascertained, checking that both the young person and their family understand the study. Those willing to take part in the study will be asked to consent to randomisation and sign the consent form. The recruiting researcher will then telephone the automated randomisation service operated by the Bristol Randomised Trials Collaboration for the intervention allocation, which will be conveyed to the participant. Allocation will be minimised [15] by age and gender, and retain a random component to reduce risk of prediction of allocation. If for any reason the service is unobtainable, randomisation will be completed during the next working day and the participant will be told of the results by phone or in person.

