### Interventions

•SMC: children and their families are offered a variety of treatment options that are recommended in NICE guidelines [2]. Typically this is centred around graded activity and involves a follow-up phone call at two weeks followed by family based rehabilitation consultations lasting one hour at approximately six weeks, three months, and four and a half months. The number and timing of the sessions are agreed with the child and family and varies depending on the needs and goals of the child. Children who have high levels of anxiety are offered three individual sessions of CBT every two weeks over a six week period. Other interventions such as graded exercise therapy (GET) [16] are available for children and young people if needed. The clinical team providing SMC are not informed by the research team to which trial arm a participant has been allocated.

•SMC plus the LP: in addition to the SMC detailed above, young people and their parents will be asked to read the information about the LP on the website [http://www.lightningprocess.com] or using information sheets. If the young person is well enough, they will be asked to read a book about the LP, given to them from the LP team, or listen to an audio book if preferable. Children/young people and their parents will be asked to complete an assessment form (which will take about ten minutes) where they are asked to identify their goals and describe what they learnt from reading the book. After this they will have a telephone call with a LP practitioner (usually approximately 20 minutes). This is used to check that the young person and their parents are happy about attending the course, checks the goals identified by the young person and is an opportunity for the young person and their parents to ask further questions. If the young person and their family are happy to continue, the young person will be given a date to attend a course.

•The course is three sessions on three consecutive days. Each session is three hours and forty-five minutes long. Group sessions will include three to five young people between 12 and 18 years of age who live within the region covered by the CFS/ME service. During the group, children and young people will receive a theory session and a practical session. The course is free to those participating in the trial.

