1. The theory session will include taught elements on the stress response, how the mind-body interacts and how thought processes can be both helpful and negative. The language used by young people will be discussed and in some cases challenged. Young people will be encouraged to think about what they may be able to take responsibility for and change. The taught sessions are followed by a group discussion.

2. The practical session is used to put some of the skills learnt into practice. Young people identify a goal they wish to achieve (such as standing for longer) and are then given alternative ways to think about and prepare for this. This involves using different cognitive (thinking) strategies before and during the period in which achieving the goal is attempted. Young people are also asked to identify a goal wherein they can practise the strategies in the afternoon or evening. This goal will usually be short but could be an activity that is up to 30 minutes long.

3. The LP practitioner will then arrange two follow-up phone calls with the young person and parents within two weeks of the course and then approximately six to eight weeks later.

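### The primary model and sample size treat LP participants as independent although LP is given in groups of three to five; if outcomes correlate within groups, the standard error is understated

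*Protocol article*

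**What the plan says.** **Delivery.** In the Interventions section of the protocol article, the LP arm attends a taught course: "The course is three sessions on three consecutive days". On its size the article says: "Group sessions will include three to five young people between 12 and 18 years of age". On its content: "The taught sessions are followed by a group discussion". SMC, which both arms receive, is not described as a group treatment. It typically consists of a phone call and "family based rehabilitation consultations lasting one hour at approximately six weeks, three months, and four and a half months", with number and timing agreed with each family.

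**Analysis.** The Data analysis section names the primary model: a comparison of the arms "using multivariable linear regression adjusting for baseline value of the outcome and minimisation variables". The Randomisation section identifies those variables: "Allocation will be minimised [15] by age and gender, and retain a random component". Course group is not among them. The sensitivity analyses listed concern missing data and compliers. A full statistical analysis plan is promised before any analysis, but it is not at hand.

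**Sample size.** The Sample size section sets its target as "a difference between the two treatment arms of 8 to 10 points on the SF-36 PCS at six months". Power is put at 90%, and alpha is 1%, two-sided. It requires 32 to 50 analysed per arm and, allowing for 10 to 20% missing outcomes, 80 to 112 recruited. Clustering, an ICC or a design effect is mentioned nowhere.

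**The concern.** Young people on the same LP course share the sessions, the discussion and the occasion, so their later scores may resemble each other more than those of participants on different courses. SMC creates no such groups. This is a partially nested design: grouping arises in one arm only.

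Ordinary linear regression computes its standard error as if every participant contributed independent information. With positive within-group correlation, the LP-arm mean is less precise than the model believes. The confidence interval for the primary comparison is then too narrow, the type I error exceeds its nominal level, and the planned number of participants gives less than the stated power once the analysis is done correctly.

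**Working it through.** **1. Is there a design effect in the stated totals?** At the lower end, 2 × 32 = 64 and 64/0.8 = 80. At the upper end, 2 × 50 = 100 and 100/0.9 = 111.1, which becomes 112 when rounded up to an even total. Both stated totals follow from loss to follow-up alone.

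**2. The per-arm numbers.** The standard deviation (SD) is not stated, so it is back-solved from n = 2(z₀.₉₉₅ + z₀.₉₀)² SD²/δ² = 2(2.576 + 1.282)² SD²/δ². Since 32 × 10² = 50 × 8² = 3,200, both ends imply the same SD, about 10.37. An assumed SD of 10.3 returns exactly 32 and 50. Power is then Φ(10/(10.3 × √(2/32)) − 2.576) = Φ(3.883 − 2.576) = 90.5%. This too needs no allowance for grouping.

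**3. Effect of grouping in the LP arm only.**
- Design effect in the LP arm: DE = 1 + (m − 1) × ICC, with m = 3 to 5 from the Interventions section.
- With equal arms, the variance of the difference is multiplied by (1 + DE)/2, and the ratio of true to model standard error is s = √((1 + DE)/2).
- Actual type I error of the uncorrected test: 2Φ(−z/s).
- Power of a test that uses the correct standard error: Φ(3.883/s − 2.576).

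The ICC values are assumptions. The sample size uses 1% alpha while the Data analysis section speaks of 95% intervals, so both levels are shown.

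| ICC (assumed) | DE, m = 3 to 5 | s | Nominal 5% runs at | Nominal 1% runs at | Power, correct analysis |
|---|---|---|---|---|---|
| 0 | 1.00 | 1.000 | 5.0% | 1.0% | 90.5% |
| 0.01 | 1.02–1.04 | 1.005–1.010 | 5.1–5.2% | 1.04–1.08% | 90.1–89.8% |
| 0.05 | 1.10–1.20 | 1.025–1.049 | 5.6–6.2% | 1.19–1.41% | 88.8–87.0% |
| 0.10 | 1.20–1.40 | 1.049–1.095 | 6.2–7.4% | 1.41–1.87% | 87.0–83.4% |
| 0.20 | 1.40–1.80 | 1.095–1.183 | 7.4–9.8% | 1.87–2.95% | 83.4–76.0% |

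Example: for m = 5 and ICC 0.10, DE = 1.40, s = √1.20 = 1.095, and 2Φ(−1.96/1.095) = 7.4%.

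**4. Check by simulation.** An unadjusted equal-variance test, with 40,000 simulated trials per setting and 32 or 50 per arm, rejected at nominal 5% in 5.5 to 6.1% of trials at ICC 0.05 and 6.0 to 7.5% at ICC 0.10. The ratio of model to true standard error at ICC 0.05 was 0.95 to 0.98.

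**5. Numbers needed to keep about 90% power at ICC 0.05.** Multiplying by 1.05 to 1.10: 32 becomes 34 to 36 (33.6 and 35.2 rounded up), and 50 becomes 53 to 55 (52.5 and 55). Recruitment becomes 68/0.8 = 85 to 72/0.8 = 90, or 106/0.9 = 118 to 110/0.9 = 123.

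**The case against.** **The analysis plan may deal with it.** The named sentence fixes the outcome, the regression family and the covariates. A group effect or robust errors could be added later without contradicting it. This stands as far as it goes: one cannot say that the final analysis will ignore grouping. But the article does name the primary estimator and gives a finished sample size. Both treat LP participants as independent, and a later analysis plan cannot put a design effect into a completed sample size.

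**The correlation is not shown.** A reader might infer that the standard errors are certainly too small, or that the test certainly exceeds its 1% level. The article does not support that, because it reports no ICC. The relevant ICC is what remains after adjustment for baseline score, age and gender, on a self-reported score six months after randomisation, with individually tailored SMC in both arms. A value near zero is plausible.

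**The effective group size may be smaller.** With 10 to 20% of outcomes missing, a course of four yields 3.2 to 3.6 analysed participants. Allocated participants who attend no course belong to no group, and the article does not say that every course member is in the trial. At m = 3.2 and ICC 0.05, s = √(1 + 2.2 × 0.05/2) = 1.027, and nominal 5% becomes 5.6%. The lower ends of the ranges are therefore the safer reading.

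**Type I error and power should not be added together.** The inflated error rates belong to the uncorrected test, and the reduced power belongs to the corrected one. Starting from exactly 90% (z = 1.282), the uncorrected test at m = 4 and ICC 0.05 keeps Φ(1.282/1.037) = 89%.

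**Conclusion.** The point holds conditionally. The stated primary model and sample size make no provision for grouping in the LP arm, and under any positive within-group correlation the standard error of the primary comparison is understated. The size is modest. For ICC 0.01 to 0.10 and groups of 3 to 5, the true standard error exceeds the model's by about 0.5 to 10%, and a nominal 5% test runs at about 5.1 to 7.4%. It would reach about 9.8% only at ICC 0.20 with groups of five.

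These figures rest on assumed ICCs, equal arms, full attendance in equal groups, a back-solved SD of about 10.3 and normal approximations. The last of these ignore the further loss of precision from estimating a variance component with few groups. The point is worth correcting because it bears on the trial's main result and the remedy is cheap, not because a large error has been shown.

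**What to change.** 1. Record the LP course group of every participant who attends.
2. Keep the baseline-adjusted comparison but allow for course group in one of two ways. One is a partially nested mixed model, with a random effect for course group in the LP arm only, participants outside any LP group (SMC arm and LP non-attenders) as singletons, and small-sample degrees of freedom (Satterthwaite or Kenward-Roger). The other is regression with group-robust standard errors and a small-sample correction. Either is defensible; name one before outcome data are seen.
3. Report the estimated ICC with its uncertainty.
4. Restate the 90% power as conditional on no LP-group correlation, or give it over an ICC range as in the table.

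The cost is one identifier and a sentence or two of analysis wording. The interval will be slightly wider and the stated power slightly lower. With 32 to 50 analysed in the LP arm there will be roughly 7 groups (32/5 = 6.4, rounded up) to 17 groups (50/3 = 16.7, rounded up), so the variance component will be imprecise and may be estimated at zero. That is a reason to fix the small-sample method in advance. If the ICC is near zero, little is lost.
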